**BLINDING / MASKING**

Randomization will be performed by the Department of Neuroscience and Imaging of the University of Chieti, which will take care of the control of all processes.

Staff blinding will be respected through the following principles: only one MD will perform the initial and final evaluation of the subjects included in the study. Operators who perform measurements with fMRI will not be aware of the subjects in the sham study and control group. None of the operators involved will be aware of the purpose and design of the study.

Subjects included in the study will not be aware of the group to which they belong considering the inclusion criteria related to osteopathic treatment.

The blinding of osteopathic operators and sham operators can not be maintained due to the active nature of the treatment.

**OUTCOMES**

*Functional Magnetic Resonance (fMRI)*

Acquisitions will be performed with a 3T MR tomograph at ITAB. The following recordings will be made with fMRI:

1) baseline

2) immediately after the first session

3) After 1 month, or at the end of the treatment period

The sequences that will be used are:

1) Eco-planar weighs in T2 * for fMRI measurements with contrast Blood Oxygenation

Level Dependent (BOLD) and Pseudo-continuous Arterial Spin Labeling (pCASL) for the Brain blood flow (CBF) measurements

2) Diffusion tensor imaging (DTI) sequences for the study of structural connectivity.

3) Spectroscopy sequences for the measurement of GABA concentrations.

The anatomical target will be the anterior insula.

*fMRI task*

A standard method to evaluate interoceptive and exteroceptive awareness will be used. This method is based on a paradigm already experimented in previous studies [27, 29, 46, 47]. This consists of three independent conditions presented in causal order for 15-20 sec each. The three conditions are: a task for IA, one for EA and a resting state period. The task of AI is to count own heart beats. EA's task is to count the rhythm of a sound stimulus, a piece of music, received in headphone. The period of fixation consists of voluntarily reducing cognitive activities to a minimum.

All the stimuli will be distinguished by a specific symbol on the display, which will also control the time for each individual task. When the task is finished, the subjects will report on a "visual analogue scale" the number of heart beats or rhythm deriving from the task.

*Diffusion Tensor Imaging (DTI)*

Structural connectivity will be investigated using the DTI, focusing on possible changes after the treatment period.

*Timing of instrumental acquisitions*

The instrumental acquisitions will last 50 minutes and will be divided as follows:

1) 5 'anatomical acquisition in T1

2) 10 'MRS

3) 10 'BOLD resting state

4) 5 'pCASL

5) 10 'DTI

6) 10 'BOLD TASK

*Questionnaires*

Patients included in the study will have to answer the following questionnaires in relation to the various times:

At inclusion

• General questionnaire with the purpose of collecting information on the social demographic status, drugs used, pain location and previous treatments.

• Temperament Evaluation of the Memphis, Pisa, Paris and San Diego - Autoquestionnaire (TEMPS-A). Self-administered questionnaire that measures temperament.

• Beck Depression Inventory - II (BDI-II), a questionnaire used as an indicator of the presence and intensity of depressive symptoms.

• Clinical scale of anxiety and depression - HADS. Questionnaire for the assessment of anxiety and depression in the non-psychiatric population.

• Short Form 36 version 2 Health Survey (SF-36v2). Generic questionnaire on the quality of life. Composed of 36 questions spread over 8 main domains. Administration occurs at inclusion and after 4 weeks [48].

Pain

• McGill pain questionnaire [49], a specific questionnaire on low back pain.

Disability

• Oswestry Disability and Pain Index [50], specific questionnaire on consequences

of lumbar pain.

• Body Awareness Questionnaire (BAQ), questionnaire to assess self awareness [51]

Next to each treatment

• McGill pain questionnaire [49]

• Oswestry disability and pain index [50]

• BDI-II

• HADS

At the end of the study period

• SF-36v2 [48]

• Satisfaction with treatment [49]

• McGill Questionnaire [49]

• Oswestry disability and pain index [50]

• Body Awareness Questionnaire (BAQ) [51]

• BDI-II

• HADS

Safety will be assessed by monitoring the adverse events reported by the patient at each manual treatment session with osteopathic modality or sham treatment. The acceptance of the treatment will be evaluated through the drop-outs and the completeness of the questions on the satisfaction of the treatment and will try to try again the OMT.

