**TYPE OF INTERVENTION**

*Study group*

Patients randomized in the study group will be treated with osteopathic modality; treatments will be performed with the following schedule: a weekly session for 4 treatments for a duration of 30 minutes. The treatments will be administered by 1 expert osteopath. The techniques used will be those of ligamentous-membranous-Guidance balancing, in line with the principles available in the literature. The treatments will be carried out at the Physical and Rehabilitative Medicine Sector of the University of Sports Medicine (CUMS) in Chieti.

*Sham control group*

Patients randomized in the sham group will receive treatment with the same timing and methodology applied to the study group. The treatments will be carried out by 1 healthcare professional with the same background. The sessions will be carried out at the Physical and Rehabilitative Medicine Sector of the University of Sports Medicine (CUMS) of Chieti.

All subjects will be asked during the treatment period (4 weeks) to avoid the use of drugs.

*Patient preparation*

Subjects will be instructed to simply keep their eyes closed, not to think about anything in particular and not fall asleep. After the session of the measurement session, the participants will be asked if they have fallen asleep during the recording, and the data of the subjects with positive and doubtful answer will be excluded from the study.

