**MRI DATA PROCESSING**

The functional, structural and spectroscopic magnetic resonance data will be analyzed with dedicated software (AFNI, FSL, JMRUI) or specifically developed at ITAB, obtaining both individual and group functional activation and connectivity maps. Differences in activity and connectivity pre / post or between groups in the insula and other regions of interest will be evaluated through linear mixed effect models.

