**STATISTIC ANALYSIS**

The lack of literature on precise estimate of the effect (effect size) of the manual treatment with osteopathic modality on the main outcome limits the calculation of the sample size. Therefore, given the lack of research measuring these effects at the brain level using fMRI, it is rather difficult to have a precise effect-size estimation. However, in general, the estimates reported in the literature for the expected effect-size with fMRI measures (eg comparison of connectivity values between different populations as in Greicius et al., 2007) indicate relatively high values (Cohen ‘s d= 1.01). This effect-size, together with an alpha and beta value of 0.05 and 0.8 respectively as usual in neuroimaging studies (Desmond et al., 2002) have been included in the R Statistical program to estimate the sample size, resulting in N=16 subjects per group.

Statistical analysis will be based on the 'intention-to-treat' and 'per-protocol' method. The statistical analysis will use the mean and standard deviation, median and percentiles, percentage points for the description of the variables of the two groups. The analyzes will be standardized by age and gender. The hypothesis H0 (null hypothesis) is the non-difference between the two groups at the end of the treatment. To test this hypothesis the assumption of the normal distribution of data through the Shapiro test will be tested first.

The analysis of residuals indicates the possible use of logarithmic transformations of the data. Subsequently the univariate analysis foresees the use of the analysis of the variance (ANOVA) for the comparison of the numerical variables, while the chi square (chi-square test) for the categorical and / or ordinal variables. Primarily used for the comparison of the two samples to the baseline, with the same method we will also analyze the data at the end of the treatment taking into account the inability to detect the independent effect of the variables on the outcome. ANCOVA will be used to explore in greater detail the treatment effect considering cofactors. Multivariate analysis will include the use of the best weighed model for confounding and interaction factors.

The level of statistical significance is established for an alpha <0.05. A post-hoc power calculation will be carried out.

Table 1. Exclusion criteria

• Subjects in acute phase,

• Subjects aged under 30 and over 50

• Associated co-morbidities (i.e. metabolic syndrome)

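### Pain, disability and mood scores are collected repeatedly, but the only post-baseline test fixed for them is an end-only ANOVA that uses neither baseline nor session scores and leaves out subjects without an end score

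*Protocol*

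**What the plan says.** **Schedule.** Under Outcomes, Questionnaires, the protocol lists McGill, Oswestry, BDI-II and HADS at inclusion, again "Next to each treatment", and again "At the end of the study period". Type of Intervention gives "a weekly session for 4 treatments for a duration of 30 minutes", in both arms.

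**Tests.** Statistic Analysis states: "The hypothesis H0 (null hypothesis) is the non-difference between the two groups at the end of the treatment". ANOVA is named for numerical variables. It is "Primarily used for the comparison of the two samples to the baseline", and then "with the same method we will also analyze the data at the end of the treatment". ANCOVA with cofactors and a multivariable model follow, with no time point and without naming the baseline score as a covariate. Means, SDs, medians and percentiles are planned "for the description of the variables of the two groups", also without a time point. Both intention-to-treat and per-protocol analyses are promised, with standardisation by age and gender.

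**Mixed models.** MRI Data Processing says that differences in activity and connectivity "will be evaluated through linear mixed effect models". Nothing extends this to the questionnaires.

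**The concern.** Four clinical scores are measured repeatedly in each subject, yet the method fixed for them looks at one occasion at a time. This has three consequences.

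- **Precision.** An end-only ANOVA does not use the subject's own baseline score, usually the strongest predictor of the end score.
- **Population.** A subject who leaves after session 3 has no end score and cannot enter an end-only ANOVA. The protocol expects some drop-out, because it uses drop-outs to judge acceptance of treatment. Followed as written, the intention-to-treat comparison of pain, disability and mood becomes a comparison of completers.
- **Use of data.** The session scores carry information on subjects who leave and on the course over treatment, but no stated comparison uses them.

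The protocol already uses a suitable class of model for its three imaging occasions. The clinical scores, with more scheduled occasions, get the weaker method.

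**Working it through.** **The plan's own figure.** The protocol's only sample-size figure concerns fMRI: d = 1.01, two-sided alpha 0.05 (sidedness assumed), power 0.8. The formula gives n = 2 × (1.960 + 0.842)² / 1.01² = 15.70 / 1.0201 = 15.4, so 16 per group, as stated (16.4 with the t distribution). The protocol plans 20 per group. There is no stated figure for the questionnaires, so what follows is a comparison of methods.

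**Inputs from the protocol.** 20 per arm; one inclusion, four session and one end assessment.

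**Assumptions (not in the protocol).**
- The six occasions are distinct and equally spaced, with SD 1 at each.
- One subject per arm (5%) leaves after each of sessions 1 to 4, so 16 of 20 have an end score (20% missing).
- Within-subject correlation is compound symmetry (CS) 0.6 or 0.7, or AR(1) 0.8 or 0.9 between neighbouring occasions. The inclusion-to-end correlation r is then 0.6, 0.7, 0.8⁵ = 0.328 or 0.9⁵ = 0.590.

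**Three analyses of the end difference.**
1. Planned ANOVA: SE = √(2/16) = 0.354 SD.
2. ANCOVA on completers, adjusted for baseline: SE = √[(2/16)(1 − r²)]. For r = 0.6 this is √(0.125 × 0.64) = 0.283.
3. Mixed model on all available occasions, with a common inclusion mean and an arm difference at each later occasion: SE from the generalised least squares variance, summed over the drop-out patterns.

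| Correlation | ANOVA | ANCOVA, completers | Mixed model | Variance, mixed vs ANOVA | Variance, mixed vs ANCOVA |
|---|---|---|---|---|---|
| CS 0.6 | 0.354 | 0.283 | 0.277 | −39% | −4% |
| CS 0.7 | 0.354 | 0.252 | 0.246 | −52% | −5% |
| AR(1) 0.8 | 0.354 | 0.334 | 0.323 | −16% | −6% |
| AR(1) 0.9 | 0.354 | 0.285 | 0.273 | −40% | −8% |

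**Where the gain comes from.** For CS 0.6 the variances are 0.125 (ANOVA), 0.080 (ANCOVA) and 0.0765 (mixed model). Baseline adjustment gives 0.045 of the total gain of 0.0485, or 93%. For AR(1) 0.8 they are 0.125, 0.1116 and 0.1045, so baseline adjustment gives 0.0134 of 0.0205, or 65%. Baseline adjustment is the larger part throughout.

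**No missing end scores.** With all 20 per arm observed at the end, the mixed model and ANCOVA have the same SE for the end difference. For CS 0.6 both give √(0.1 × 0.64) = 0.253. The session scores then add nothing to that estimate.

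**Average over session 2 to end.** The mixed model gives an SE of 0.175 to 0.244 SD. This estimates a different quantity from the stated null hypothesis and is not a like-for-like gain.

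**Drop-out bias, illustration only.** If 20% of one arm lacked an end score and would have scored 0.5 SD worse than that arm's completers, the completer mean would be off by 0.2 × 0.5 = 0.1 SD. That is under a third of the ANOVA standard error of 0.354 SD.

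**The case against.** **The session scores are not excluded from analysis.** A reader might infer that they are never analysed. The protocol does not support that: the descriptive statistics, ANCOVA and multivariable model carry no time limit, and no sentence rules these scores out. What is missing is a stated comparative role. This objection stands and sets the wording of the point.

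**The count of unused assessments is not fixed.** A reader might also infer that four of six assessments, or 40 × 4 × 4 = 640 completions, go unused. The protocol does not say whether the first and last session scores double as the inclusion and end scores. If both do, there are four distinct occasions and two intermediate ones. The 640 also assumes that everyone completes everything. Neither figure should be relied on.

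**Modelling of secondary scores belongs in a statistical analysis plan.** Often so, and such a plan could also supply a method for missing scores. But the protocol is not silent here: it names a method and a time point for the end comparison, and that choice can be questioned. Testing at the end does match the stated null hypothesis, so there is no contradiction on timing.

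**ANCOVA is already planned.** If it adjusted for baseline it would secure most of the precision. As written it is exploratory, does not name the baseline score, and on the end score it has the same limit for subjects who leave.

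**Drop-out is assumed.** Correct. Stopping treatment is also not the same as missing the end questionnaire, and the protocol does not announce a complete-case analysis. The restriction follows from the method: an end-only ANOVA without imputation has no place for a missing end score.

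**The stakes are limited.** The questionnaires appear in neither the main aim nor secondary goals I to VI. This stands.

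**Conclusion.** The point holds in a limited form. For McGill, Oswestry, BDI-II and HADS, the one post-baseline test fixed with a time point leaves out the baseline score, gives the session scores no stated comparative role, and does not accommodate subjects without an end score, despite the intention-to-treat promise.

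Under the stated assumptions on correlation and 20% missing end scores, a mixed model lowers the SE of the end difference from 0.354 SD to between 0.246 and 0.323 SD, a variance reduction of 16 to 52%. Most of this is baseline adjustment. The session scores themselves add 4 to 8% in variance relative to ANCOVA on completers, and nothing if no end scores are missing. They reduce drop-out bias only if leaving is explained by scores already observed.

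The consequence is confined to secondary clinical outcomes. The MRI aim and the sample size do not change.

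**What to change.** In Statistic Analysis, replace the end-only ANOVA for McGill, Oswestry, BDI-II and HADS with one linear mixed model per score, the class already named in MRI Data Processing. Specify:

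- all available occasions of all randomised subjects, including those without an end score;
- a common pre-treatment mean for the two arms, with arm-by-occasion terms afterwards;
- the arm difference at the end as the main estimate, to match the stated null hypothesis;
- the average arm difference over sessions as supportive.

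State that validity with missing end scores rests on drop-out being explained by observed scores.

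The cost is a few sentences of analysis wording. No visit, questionnaire, assessment time or sample size changes. When the model is written, the occasions should be labelled as the existing schedule has them, including whether the first and last session scores are separate from the inclusion and end scores.

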**PROCEDURE FOR DATA COLLECTION AND TREATMENT**

Data collection will be performed using a specific software, developed ad-hoc for the purpose of the study.

The data will be processed according to the privacy law. All information will be encrypted, coded and made anonymous. The acquired data will be used exclusively for the specific purpose of the research.

**ETHICS COMMITTEE, INFORMED CONSENT and REGISTRATION TRIAL**

Eligible subjects will be required to provide informed consent, in accordance with the Helsinki Declaration, to enter the trial. This protocol will be registered on www.clinicaltrial.gov, only after the approval of the ethics committee.

**MRI DATA PROCESSING**

The functional, structural and spectroscopic magnetic resonance data will be analyzed with dedicated software (AFNI, FSL, JMRUI) or specifically developed at ITAB, obtaining both individual and group functional activation and connectivity maps. Differences in activity and connectivity pre / post or between groups in the insula and other regions of interest will be evaluated through linear mixed effect models.

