
MATERIALS AND METHODS

PURPOSE OF THE STUDY

The main aim of the present randomized controlled two-arm and single-blind study is to evaluate the change in activation and connectivity of the anterior cortex of the insula and the medial prefrontal cortex between before and after the period of manual treatment with osteopathic modality. Secondary goals are:

I) to monitor the differences of activity and FC of the SN between the study group and the sham control;

II) to monitor the intra-group differences and the intergroup of activities and of the CF of the SN immediately after the first treatment;

III) to monitor the differences in activity of intra-group and inter-group RSN during the treatment period;

IV) to monitor the differences in the IA and EA both within and between groups;

V) to evaluate the DTI structural differences;

VI) to evaluate differences in terms of GABA concentration in the anterior insula by means of

MRS

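### The MRI mixed-model sentence does not tie its comparisons to the end-of-treatment null hypothesis or bring the baseline scan into the treatment contrast

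*Protocol*

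**What the plan says.** The protocol's section on MRI data processing is the only place that assigns a method specifically to the MRI data: "Differences in activity and connectivity pre / post or between groups in the insula and other regions of interest will be evaluated through linear" (the sentence ends by naming mixed models). It lists no fixed effects and names no scan.

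The Outcomes section schedules three scans: at baseline, "immediately after the first session", and at the end of the treatment period.

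The Statistic Analysis section fixes the hypothesis: "The hypothesis H0 (null hypothesis) is the non-difference between the two groups at the end of the treatment". It plans ANOVA on the end-of-treatment data, then ANCOVA with cofactors that are not named. Interaction is mentioned only in general terms, for the multivariate analysis.

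The stated main aim concerns change over time: "evaluate the change in activation and connectivity of the anterior cortex of the insula and the medial prefrontal cortex between before and after" treatment. The sham comparison appears as secondary goal I: "to monitor the differences of activity and FC of the SN between the study group and the sham control".

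The sample size rests on published fMRI effect sizes that "indicate relatively high values (Cohen ‘s d= 1.01"), taken from a "comparison of connectivity values between different populations".

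**The concern.** With three scans per subject, a between-group comparison that names no scan has no defined target. It could mean the difference at the final scan, which is what the null hypothesis asks, or a difference averaged over scans. Randomisation makes the expected group difference at baseline zero, so an average that includes the baseline scan shrinks a real end-of-treatment effect.

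The pre/post comparison has a different weakness. Whether taken within the osteopathic arm or over both arms, it contains no comparison with sham. Scanner habituation, task practice or natural course can move it without any treatment effect. Because the sentence joins the two comparisons with *or*, and the main aim is itself worded as a before/after change, an analysis that reported only a pre/post change would comply with the protocol.

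Finally, the baseline scan is collected but is nowhere named as an adjustment variable, so available precision may go unused.

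**Working it through.** **Inputs from the protocol.** d = 1.01; alpha 0.05; power 0.80 (the text calls this beta); 16 per group calculated, 20 per group planned; three scans.

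**Assumptions.** Two-sided test; unit SD at each scan; the same correlation ρ between any two scans (the documents give none, so a range is shown); no expected group difference at baseline; no drop-out.

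**1. The plan's own figure.** n = 2(1.960 + 0.842)²/1.01² = 15.4, so 16 per group, as stated. The exact t test needs 17 and has 78.9% power at 16. At the planned 20 per group, a comparison of the final scan alone has 87.5% power, whatever ρ is.

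**2. Group effect averaged over three scans (one possible reading).** Let k be the share of the effect already present at the second scan. The expected difference is 1.01(1 + k)/3 and the SD of a three-scan mean is √((1 + 2ρ)/3). Example with ρ = 0.6, SD 0.856: the differences 0.337, 0.505 and 0.673 become standardised effects of 0.393, 0.590 and 0.786. Power by noncentral t, 20 per arm:

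| ρ | k = 0 | k = 0.5 | k = 1 |
|---|---|---|---|
| 0.4 | 26.8% | 52.0% | 76.4% |
| 0.6 | 22.8% | 44.4% | 67.8% |
| 0.8 | 20.0% | 38.7% | 60.6% |

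If only the baseline and final scans enter, the effect is 0.505/√((1 + ρ)/2), and power is 46.0% at ρ = 0.4 and 37.5% at ρ = 0.8.

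**3. Pre/post change when there is no treatment effect.** Take a drift of m SD common to both arms. The noncentrality is m√N/√(2(1 − ρ)).
- Both arms pooled (N = 40, 38 df): significant in 46% of trials at m = 0.3, ρ = 0.5, rising to 98% at m = 0.5, ρ = 0.7.
- Within one arm (N = 20, 19 df): 25% to 78% for the same two cases.

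The drift sizes are assumed; the documents give none.

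**4. Contrasts that answer the null hypothesis.** Standardised effects: final scan alone 1.01; change score 1.01/√(2(1 − ρ)); baseline-adjusted 1.01/√(1 − ρ²), with one df fewer. Power at 20 per arm:

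| ρ | Final scan alone | Change score | Baseline-adjusted |
|---|---|---|---|
| 0 | 87.5% | 59.5% | 87.5% |
| 0.3 | 87.5% | 74.9% | 90.3% |
| 0.5 | 87.5% | 87.5% | 94.9% |
| 0.7 | 87.5% | 98.0% | 99.2% |
| 0.8 | 87.5% | 99.8% | 99.9% |

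The change score is weaker than the final scan alone below ρ = 0.5. Baseline adjustment is essentially never weaker.

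**The case against.** A reader might infer that the mixed model is set up with only group and time main effects, and so loses most of the trial's power. The documents do not support that. The sentence lists no model terms, does not exclude an interaction, and does not say that the group difference is averaged over scans.

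Other parts of the protocol point to a milder reading. The null hypothesis concerns "the non-difference between the two groups at the end of the treatment", a comparison at one time. Secondary goals II to IV pair within-group with between-group differences, so the MRI sentence may be shorthand for that pair rather than for a time effect pooled over arms. The planned end-of-treatment ANOVA answers the null hypothesis directly and has 87.5% power at 20 per arm. It would also be wrong to say that only a group-by-scan term can test that hypothesis. Finally, the full list of model terms is commonly left to a statistical analysis plan, which is not at hand.

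All of this stands, and it removes the claim that the trial is underpowered as written. It does not remove the narrower point. The protocol does name the MRI comparisons, and it names them without a scan, without a link to the null hypothesis and without the baseline scan. An analysis plan that followed the sentence literally could report a pre/post change as the result. The statistical section does not close the gap, because its ANCOVA cofactors are unnamed and it does not say how its analyses relate to the mixed models.

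**Conclusion.** The point holds in a limited form and is of moderate severity. The MRI sentence leaves the treatment contrast open, permits a pre/post change to stand as the result, and makes no stated use of the baseline scan. The 20-76% power range applies only if the group effect is averaged over all three scans, with ρ assumed at 0.4-0.8, and should not be cited as the power of the planned analysis. The comparison that the null hypothesis implies has 87.5% power. What the plan forgoes by not specifying baseline adjustment is the step from 87.5% to about 90% at ρ = 0.3, 95% at 0.5 and 99% at 0.7. These figures take d = 1.01 as given, although it comes from a comparison of populations and not from a treatment effect.

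**What to change.** In the MRI data processing section, state that:
- the treatment effect is the between-group difference at the end-of-treatment scan, adjusted for the baseline scan, either with baseline as a covariate or in a mixed model with group-by-scan terms and a common baseline mean;
- the same contrast at the second scan serves the between-group part of goal II;
- overall group effects and pre/post changes are descriptive and are not evidence of a treatment effect.

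Refer from there to the null hypothesis in the Statistic Analysis section. An unadjusted change score should not be the chosen form, since it loses to the final-scan comparison when the correlation is below 0.5. The cost is two or three sentences, with the same scans, software and sample size.

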
The correlations between the various brain areas appear to be exclusive. In fact, the individual structures of each network seem to be anti-correlated. This reinforces the idea that the two portions of the insula underlie different functions and are connected to different networks that work independently [17].

One way to measure the functional connections between the various brain areas is during the "resting state" condition, in which the subject is in the absence of stimuli. Fluctuations of brain activity are recorded using fMRI with BOLD technique [18]. This allows to highlight spontaneous activity patterns known as resting state networks (RSN) [13, 17, 19, 20]. The properties of the BOLD signal of the RSN seem to be consistent between individuals and stable between different measurement sessions [21-23]. The SN and therefore the insula circuits have also been studied in the field of RSN, with more precise areas of brain involvement [11, 12]. Menon and Uddin have hypothesized that the right anterior insula acts as a causal center of efference that coordinates two important networks of executive (external, posterior insula) and interoceptive (internal, anterior insula) control [11]. Thus the connection hypotheses formulated by Craig [1-3, 24] as well as the SN [11, 12] define the role of the right insular cortex as a pivotal region in the brain's attentive system [25, 26].

Moreover, some authors have studied the activation of the insula cortex in relation to specific tasks: interoceptive (heartbeat [27] or breath [28]) and exteroceptive [29], showing significantly different behaviors.

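### The main aim concerns the anterior insula and the medial prefrontal cortex, but the MRI analysis is written for the insula and an open list of other regions

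*Protocol*

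**What the plan says.** Three sections of the protocol bear on which brain regions carry the main result.

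- **Purpose of the study.** The main aim is the "change in activation and connectivity of the anterior cortex of the insula and the medial prefrontal cortex", before against after treatment. That is two regions and two measures. Secondary goals I to III concern the salience network and resting-state networks. Secondary goal VI is "to evaluate differences in terms of GABA concentration in the anterior insula by means of" spectroscopy.
- **Outcomes.** After the list of sequences, whose last item is GABA spectroscopy, comes the sentence "The anatomical target will be the anterior insula". It does not say whether it covers every sequence or only spectroscopy. Resting-state and task BOLD runs are scheduled with no stated restriction to the insula.
- **MRI data processing.** The data are processed "obtaining both individual and group functional activation and connectivity maps", and differences over time or between groups "in the insula and other regions of interest will be evaluated through linear mixed effect models".

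The medial prefrontal cortex appears in the background and in the main aim, and is not named in the outcome or analysis sections. The background also says that "the two portions of the insula underlie different functions and are connected to different networks that work independently".

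The Statistic analysis section has one effect size (d = 1.01, from a comparison between populations, tied to no region), one significance level of 0.05, and a result of 16 per group. Planned enrolment is 20 per group.

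**The concern.** A reader who takes the main aim to the analysis section finds a different set of regions. One of the two main-aim regions is not named. The other has been widened from the anterior insula to the insula, although the background treats the anterior and posterior parts as functionally distinct. The remaining regions are left open.

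Two analysts could both follow the protocol and report different main results, one following the aim and the other the analysis section. Because the list is open, the medial prefrontal result could be presented as part of the main finding, or left among the other regions, once the maps have been seen. That is a route to selective reporting. It also leaves unclear how many tests share the single 0.05 level, while the sample size was computed for one.

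**Working it through.** **Step 1. Compare the sections.**

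| Section | Insula | Medial prefrontal cortex | Other regions |
|---|---|---|---|
| Purpose (main aim) | anterior | named | none |
| Outcomes (target sentence) | anterior | not named | none |
| MRI data processing | not restricted to anterior | not named | open list |

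If the target sentence in Outcomes refers only to spectroscopy, it agrees with secondary goal VI and drops out of the comparison. The first and third rows still differ.

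**Step 2. Reproduce the stated sample size.** Inputs from the Statistic analysis section: d = 1.01, alpha = 0.05, and the 0.8 labelled beta, read as power. A two-sided test is assumed, as the section does not say.

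n per group = 2 × (1.960 + 0.842)² / 1.01² = 15.4, rounded up to 16. This matches the protocol. The two-sample t-test gives 16.4, so 17. The figure is for one test in one region on one measure.

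**Step 3. Count the tests in the main aim as worded.** Two regions give two tests if one measure is chosen. Two regions × two measures give four.

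**Step 4. False-positive rate if each test is run at 0.05.** Independence is assumed:

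- two tests: 1 − 0.95² = 0.0975
- four tests: 1 − 0.95⁴ = 0.185

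**Step 5. Power at 20 per arm if alpha is shared equally (Bonferroni).** Assume d = 1.01 for every test and usable scans from all 20 per arm. The noncentrality is 1.01 × √(20/2) = 3.19. Power and the n for 80% power are from the two-sided t-test, with the normal approximation in brackets.

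| Tests | Alpha per test | Power per test at 20 per arm | n per arm for 80% |
|---|---|---|---|
| 1 | 0.05 | 0.88 (0.89) | 17 (16) |
| 2 | 0.025 | 0.80 (0.83) | 20 (19) |
| 4 | 0.0125 | 0.71 (0.76) | 24 (22) |

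If only the computed 16 per arm gave usable scans, t-test power per test would be 0.69 for two tests and 0.58 for four.

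**The case against.** The strongest reply is that this is loose wording rather than a flaw. The sentence under MRI data processing is a general one that serves all the MRI aims. The secondary goals on the salience and resting-state networks need regions beyond the two in the main aim, so an open list is natural. Insula may be shorthand for anterior insula, since the background speaks of insula activity and the anterior circuit together. Masks and similar detail commonly belong in a statistical analysis plan, which is not at hand.

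Much of this stands. Mask definitions can wait, and the reference to other regions is not evidence of an intention to drop the medial prefrontal cortex. But which regions carry the main aim is something the protocol has itself stated, and its only MRI analysis rule states it differently. A later plan would have to choose between them.

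Two stronger readings are tempting and should not be drawn:

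- **That an anterior-insula effect is diluted by the posterior insula.** This would happen only if a whole-insula measure were used and the posterior part responded less or in the opposite direction. No section averages the two parts or defines a composite, and mixed models fitted to separate regions do not pool them. A power loss would also need a posterior effect and a between-patient correlation of regional values. The background's remarks on independent networks give neither.
- **That the medial prefrontal half of the main aim has no measure.** BOLD activation and connectivity maps are planned and can cover it. It is unnamed in the analysis, not unmeasured.

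**Conclusion.** The point holds as an inconsistency in the main-aim regions. The aim specifies the anterior insula and the medial prefrontal cortex; the analysis section specifies the insula and an unnamed remainder. This allows the main result to come from a different or later-chosen region. The target sentence in Outcomes is ambiguous, but the conclusion does not depend on it.

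The mismatch itself has no computable effect on power. The multiplicity behind it has a size: a false-positive rate of 9.8% to 18.5% if two to four tests are each run at 0.05, or power per test of about 80% to 71% at 20 per arm if alpha is shared. These figures assume independent tests for the error rates, and d = 1.01 for every test with complete data for the power. The protocol ties that effect size to neither region nor measure, so the figures are illustrations. The change is worth making before arm-labelled data are seen, because it removes room for selection at little cost.

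**What to change.** 1. **MRI data processing:** state that the main-aim analysis uses the anterior insula and the medial prefrontal cortex, with masks fixed before any arm-labelled data are seen. Assign the remaining regions, including the posterior insula and the salience and resting-state network regions, to the secondary goals, or label them exploratory.
2. **Outcomes:** say whether the anterior insula target applies to spectroscopy only. If it does not, name both main-aim regions as BOLD targets.
3. **Statistic analysis:** name one primary region and one primary measure (activation or connectivity), or state how the 0.05 level is shared.

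Steps 1 and 2 cost wording and a set of masks, with no extra scanning. Under step 3, a single primary test keeps the existing sample-size basis. Two tests with shared alpha just about reach 80% power at 20 per arm. Four would need 22 (normal approximation) to 24 (t-test) per arm for 80%, or acceptance of about 71% by the t-test. The downside is that other regions can no longer be promoted to main results.
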